**Methods/Design:**

In a randomised trial we will compare (a) computerised cognitive behavioural therapy with (b) treatment as usual by a GP, and (c) computerised cognitive behavioural therapy in combination with usual GP care. Three hundred mild to moderately depressed patients (aged 18–65) will be recruited in the general population by means of a large-scale Internet-based screening (*N *= 200,000). Patients will be randomly allocated to one of the three treatment groups. Primary outcome measure of the clinical evaluation is the severity of depression. Other outcomes include psychological distress, social functioning, and dysfunctional beliefs. The economic evaluation will be performed from a societal perspective, in which all costs will be related to clinical effectiveness and health-related quality of life. All outcome assessments will take place on the Internet at baseline, two, three, six, nine, and twelve months. Costs are measured on a monthly basis. A time horizon of one year will be used without long-term extrapolation of either costs or quality of life.

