### Study population

The patient population we aim to investigate consists of 300 mild to moderately depressed adults. Patients are eligible to participate if they meet the following criteria: age 18 to 65 years; access to the Internet at home; at least mild to moderate depressive complaints (BDI-II score > 16), although a DSM-III-R diagnosis of major depression was not required; duration of depressive complaints 3 months or more; no current psychological treatment for depression; no continuous antidepressant treatment for 3 months or more prior to entry; fluent in Dutch language; no alcohol and/or drug dependence; and no severe psychiatric co-morbidity (e.g. psychotic disorders).

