### Randomisation and procedure

Randomisation will take place after informed consent is obtained. An independent statistician will develop the randomization code. Block randomization will be used to ascertain that each intervention consists of equally large groups. The randomization code will be given to an independent IT-specialist who will develop a computer program to carry out the group allocation. On entry into the trial the computer program provides the next available number. The randomization code will not be revealed until participant inclusion is complete. In view of the nature of the treatments, blinding of the participants and researchers is not possible.

Baseline assessment will take place at the research centre before randomization. The questionnaires will be administered on a computer. All follow-up assessments will take place at home via the Internet at two, three, six, nine and twelve months after inclusion. Preceding an upcoming assessment point, participants will receive an email alert. If a participant fails to complete the assessment within one week, an email-reminder will be sent. When the participant still fails to fill out the questionnaires, a phone call will be made.

Individuals will not be paid for participation, but will receive a small fee for Internet use.

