### Analyses

#### Clinical analyses

Data-analysis will include intention-to-treat analysis and per-protocol analysis. Analysis will include elementary head-to-head comparisons of the intervention groups as well as more complicated multi-level analysis incorporating patients and time measurements if necessary. An integrity check and a process evaluation will be performed using qualitative methods of analysis. In case of missing data, we will impute intermittent missing data using the mean of the values of a previous and a subsequent time point. Other missing data (i.e. missing values due to lost to follow-up) will only be imputed when more then 15% of the data are missing.

To test the main hypotheses, difference scores for all outcome variables will be calculated (t_0 _minus t_k_) and compared between the three groups using ANOVA. In case of violation of assumptions, robust ANOVA can used [71]. We will then compute improvement effect sizes and between-group effect sizes [72] or robust equivalents [see [73]]. Next, we will calculate the number of patients who showed reliable and clinically significant change on the BDI-II using the method of Jacobson and Truax [74]. This calculation is based on two components: (1) the extent to which the pre-to-post-difference score is reliable taking into account the measurement variability of the instrument (reliable change; RC), and (2) the extent to which post-treatments scores are clinically meaningful (clinically significant change; CSC) [75]. Chi-square tests will be used to test the frequency differences in RC, CSC and RC+CSC between the three groups.

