#### Economic evaluation

Since the follow-up period lasts one year and no extrapolation over time will be executed, discounting of costs is not necessary. All costs will be indexed to the year 2007 by means of the price indexes of the Dutch Central Bureau of Statistics (CBS).

For each patient, volumes of care, travels, lost time for receiving care and lost productivity hours will be multiplied by the prices determined for each cost item. Based on the costs per item, costs during the follow-up period will be calculated as the cumulative costs per patient. The costs at baseline and during the follow-up period of the three groups will be compared by the non-parametric bootstrapping method with confidence intervals in percentiles. By bootstrapping, samples of the same size as the original data are drawn with replacement from the observed data [76]. The quality of life and clinical outcome variables will be compared between the three groups at baseline and during the follow-up period using ANOVA.

In case of baseline differences of costs, effectiveness, or utility scores between the patient groups, corrections will be performed [77-79]. The economic evaluation will consist of a base-case cost-effectiveness and cost-utility analysis, and sensitivity analyses. Uncertainty of parameter estimates of the base-cases will be dealt with by these sensitivity analyses [52]. In the base-cases, data will be analysed according to the intention-to-treat principle. Incremental cost-effectiveness ratios (ICERs) will be determined on the basis of incremental costs and incremental effects [52] of (a) stand alone CCBT compared with (b) usual GP care, or (c) a combination of CCBT and usual GP care. The primary outcome measure for the cost-effectiveness analysis is depression measured by the BDI-II, and for the cost-utility analysis the QALY based on the EQ-5D. The cost-effectiveness ratio will be stated in terms of costs per point improvement on the BDI-II, the cost-utility ratio will focus on the net cost per QALY gained. In our primary analysis QALYs will be derived from the EQ-5D using the UK-tariff. Scores on the quality of life domains derived from the WHOQOL-BREF and the sixth domain of the EQ-5D+C will be used to provide in-depth insight into the quality-of-life.

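### The main hypotheses are tested on raw change scores without a baseline covariate, and baseline correction in the economic evaluation is conditional on observed differences

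*Protocol article*

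**What the plan says.** The Abstract (Methods/Design) states: "Primary outcome measure of the clinical evaluation is the severity of depression". The BDI-II measures it.

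Analyses, Clinical analyses, fixes the test: "To test the main hypotheses, difference scores for all outcome variables will be calculated" as baseline minus follow-up "and compared between the three groups using ANOVA". A robust ANOVA is the fallback if assumptions fail. No covariate is named for either. The section also mentions "more complicated multi-level analysis incorporating patients and time measurements if necessary", again without a baseline covariate.

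The covariate exists for everyone. Randomisation and procedure says: "Baseline assessment will take place at the research centre before randomization". Table 1 marks the BDI-II at baseline and at all five follow-ups, and Study population makes a BDI-II above 16 an entry condition.

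Analyses, Economic evaluation, compares the arms at baseline, using bootstrap percentile intervals for costs and ANOVA for quality of life and clinical outcomes. It then says: "In case of baseline differences of costs, effectiveness, or utility scores between the patient groups, corrections will be performed". Three references are cited for the correction. The text does not say how large a difference has to be.

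**The concern.** A change score uses the baseline value but assumes that each extra point at baseline carries through as exactly one extra point at follow-up. ANCOVA estimates that slope. If the true slope is not 1, the change score has two costs. It carries variance that ANCOVA would remove, and it wrongly corrects any chance imbalance between arms.

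In the economic evaluation the issue is discretion. Any three randomised arms differ somewhat at baseline, so a rule that applies only if they differ leaves the analyst to decide, with the data in view, whether to adjust. That decision feeds the ICER, the acceptability curve and the net monetary benefit. A QALY total adds up utility over time and does not subtract the starting level, so an uncorrected baseline utility gap passes into the QALY difference.

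**Working it through.** **Inputs.** From Sample size: difference in change scores 5, SD 5.25, 84 per group, 100 after 20% withdrawal, hence 100 × 0.8 = 80 completers per arm. The documents do not give r or k. Both are assumptions and are shown as ranges.

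**The plan's own figure.** With 5, SD 5.25, 90% power and two-sided alpha 0.05, the required size is 2 × (1.960 + 1.282)² × (5.25/5)² = 23.2, so 24 per group, not 84. The 84 corresponds to a standardised effect of about 0.50, against the stated 5/5.25 = 0.95. That discrepancy is a separate matter. Here it means only that power is a poor scale for the gain, because at the stated inputs 80 per arm already gives power above 99.99%.

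**Variance ratio.** With baseline variance set to 1:
- change score: 1 + k² − 2rk
- ANCOVA: k²(1 − r²)
- ratio: k²(1 − r²) / (1 + k² − 2rk)

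The first variance minus the second is (1 − rk)², where rk is the slope on baseline. This is never negative, and it is zero only if the slope is 1.

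| k | r = 0.3 | r = 0.5 | r = 0.7 |
|---|---|---|---|
| 0.8 | 0.50 | 0.57 | 0.63 |
| 1.0 | 0.65 | 0.75 | 0.85 |
| 1.25 | 0.78 | 0.89 | 0.98 |
| 1.5 | 0.87 | 0.96 | 0.998 |

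A simulation of three arms of 80 at k = 1 gave 0.67, 0.74 and 0.84, with both estimators unbiased.

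The extra patients that change scores need for equal precision are 1/ratio − 1. That is 54%, 33% and 18% at k = 1, but 15%, 4% and 0.2% at k = 1.5.

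**Interval width.** With SD 5.25 and 80 per arm, the 95% half-width for a two-arm difference in change is 1.96 × 5.25 × √(2/80) = 1.63 BDI-II points. Multiplying by the square root of the ratio gives 1.31 to 1.50 at k = 1, and 1.52 to 1.63 at k = 1.5.

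**Shift under chance imbalance.** If two arms differ by D at baseline and the slope is b, the change-score contrast is shifted by (1 − b)D. Assume a baseline SD of 7 to 10. One standard error of imbalance is then SD × √(2/80), or 1.1 to 1.6 points. With b = 0.5 the shift is about 0.6 to 0.8 points, against a target difference of 5.

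**Effect of the entry cut-off.** Take an assumed baseline mean of 20, SD 10, slope 0.5 and residual variance 75. Before selection the ratio is 75 / (0.25 × 100 + 75) = 0.75. Restricting to scores above 16 leaves the slope at 0.5 and lowers the baseline SD to about 6.8, so the ratio becomes 75 / (0.25 × 46 + 75) = 0.87. The cut-off shrinks the gain.

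**QALYs.** Table 1 has the EuroQol at 0, 3, 6, 9 and 12 months. Assuming linear interpolation, baseline has weight 0.125 year and follow-up 0.875 year. If a fraction c of a baseline gap g persists through follow-up, the QALY gap is g(0.125 + 0.875c), which lies between 0.125g and g for c from 0 to 1. For each 0.01 of baseline utility gap, that is 100 to 800 currency units of net monetary benefit at the document's upper threshold of 80,000 per QALY.

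**The case against.** The strongest reply is that the plan is valid as it stands. Randomisation makes change-score ANOVA unbiased with correct type I error, it already uses baseline, and it matches a sample size set in change scores. All of that stands. A reader might infer that the primary test is biased or invalid, and it is not. The shift calculated above is conditional on a chance imbalance and averages to zero over randomisations.

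Three further readings are tempting, and the documents do not support them:
- That the BDI-II entry cut-off drives the slope well below 1. Selecting on the covariate leaves a linear slope unchanged and, by narrowing the baseline SD, reduces the benefit of ANCOVA. The slope may be below 1 for other reasons, but the documents give no figure.
- That the trial forfeits a large amount of power. This needs a standardised effect near 0.50, which the plan does not state, and the familiar (1 + r)/2 formula, which needs equal SDs.
- That the economic rule invalidates nominal error rates. No significance trigger is named, the method of correction is left to cited sources, and the outputs (ICER, acceptability curve, net monetary benefit) are not tests at a nominal alpha.

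It can also be said that covariates belong in an analysis plan that is not shown. That would answer a silent article. This article names the test of its main hypotheses and the condition for economic correction, so both are stated choices. The multi-level model is mentioned only as an option.

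**Conclusion.** The point holds as a weakness in efficiency and prespecification, not as an error of validity. Unadjusted change-score ANOVA has no precision advantage over ANCOVA in large samples. Estimating the slope costs one degree of freedom out of roughly 240. Across r from 0.3 to 0.7, adjustment would cut the variance by 15% to 35% if the SDs are equal, and by 0.2% to 13% if the follow-up SD is 1.5 times the baseline SD. Which end applies cannot be settled from the documents. The interval narrows, or stays essentially the same, whatever the true treatment effect.

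The conditional correction in the economic evaluation is a matter of analyst discretion. With no threshold, two analysts could reach different ICERs from the same data. The QALY illustration rests on linear interpolation and on the fraction of the gap that persists. That a baseline utility gap enters the QALY difference does not depend on the exact values.

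**What to change.** - **Clinical analyses:** make the main analysis an ANCOVA, or the multi-level model already named, with the outcome's own baseline value as a prespecified covariate whatever imbalance is observed. Using follow-up or change as the dependent variable gives the same treatment estimate once baseline is in the model. Keep change-score ANOVA as supportive.
- **Economic evaluation:** always adjust QALYs for baseline utility and costs for baseline costs, by regression within each bootstrap sample. For the BDI-II effect in the ICER, adjust for baseline BDI-II as in the clinical analysis. Delete the condition that correction follows only from observed differences. Baseline comparisons can remain as description, without deciding the model.

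The cost is wording in the analysis plan. The BDI-II and EuroQol are collected at baseline, and the plan already intends to compare baseline costs, so no new data, visits or patients are needed.

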#### Economic evaluation

Since the follow-up period lasts one year and no extrapolation over time will be executed, discounting of costs is not necessary. All costs will be indexed to the year 2007 by means of the price indexes of the Dutch Central Bureau of Statistics (CBS).

For each patient, volumes of care, travels, lost time for receiving care and lost productivity hours will be multiplied by the prices determined for each cost item. Based on the costs per item, costs during the follow-up period will be calculated as the cumulative costs per patient. The costs at baseline and during the follow-up period of the three groups will be compared by the non-parametric bootstrapping method with confidence intervals in percentiles. By bootstrapping, samples of the same size as the original data are drawn with replacement from the observed data [76]. The quality of life and clinical outcome variables will be compared between the three groups at baseline and during the follow-up period using ANOVA.

In case of baseline differences of costs, effectiveness, or utility scores between the patient groups, corrections will be performed [77-79]. The economic evaluation will consist of a base-case cost-effectiveness and cost-utility analysis, and sensitivity analyses. Uncertainty of parameter estimates of the base-cases will be dealt with by these sensitivity analyses [52]. In the base-cases, data will be analysed according to the intention-to-treat principle. Incremental cost-effectiveness ratios (ICERs) will be determined on the basis of incremental costs and incremental effects [52] of (a) stand alone CCBT compared with (b) usual GP care, or (c) a combination of CCBT and usual GP care. The primary outcome measure for the cost-effectiveness analysis is depression measured by the BDI-II, and for the cost-utility analysis the QALY based on the EQ-5D. The cost-effectiveness ratio will be stated in terms of costs per point improvement on the BDI-II, the cost-utility ratio will focus on the net cost per QALY gained. In our primary analysis QALYs will be derived from the EQ-5D using the UK-tariff. Scores on the quality of life domains derived from the WHOQOL-BREF and the sixth domain of the EQ-5D+C will be used to provide in-depth insight into the quality-of-life.

Non-parametric bootstrap re-sampling techniques will be used to explore uncertainty around estimates of cost-effectiveness derived from the study sample [76]. Decision uncertainty will be represented graphically by means of a cost-effectiveness acceptability curve (CEAC) [52,80,81]. In addition, the net monetary benefit (NMB) will be used to present the cost-effectiveness and cost-utility results in monetary units. The NMB expresses the difference in effects between the intervention groups in monetary values using the threshold willingness-to-pay for a unit of effect, minus the difference in costs between the interventions [52,82]. Since the value that society would place on a unit reduction in BDI-II depression score is unknown, different values will be assumed to calculate the NMB [27]. Regarding the QALY, the Dutch Council of Public Health and Care suggested in 2006 a ceiling of £80.000 per QALY per year [83]. Alternative values, ranging to £80.000 per QALY, will be used to estimate the NMB.

The alternative threshold values of the NMB will be analysed in sensitivity analyses. Other aspects that can be part of a sensitivity analysis are: varying the utility outcome measure by using the SF-6D or alternative tariffs to value the EQ-5D utility (Dutch tariff instead of the UK tariff), or including other effectiveness measures used in the clinical evaluation. Cost prices will be varied as minimum and maximum cost price estimates. Next to the intention-to-treat analysis, a per-protocol analysis can be performed.

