### Current study

In the present study we aim to evaluate the (cost-) effectiveness of online CCBT for mild to moderate depression in primary care. In a randomised trial we will compare (a) CCBT with (b) treatment as usual (TAU) by a GP, and (c) CCBT in combination with TAU. In a recent Dutch study of Spek et al. (2007), the same CCBT program has shown to be equally effective as group CBT in people over 50 years old with subthreshold depression [28]. Based on the results from a recent systematic review [23] we hypothesise that CCBT will be more effective than TAU by a GP. Furthermore, we hypothesise that CCBT in combination with TAU will be more effective than CCBT alone by increasing treatment adherence. Although some studies have shown that for mild depression a combination of pharmacotherapy and psychotherapy does not appear more effective than psychotherapy alone [29], other studies suggested that patients receiving combined treatments were more likely to stay in treatment and comply to the treatment protocol [30].

Regarding the economic evaluation we hypothesise the following. The self-help intervention CCBT alone implies costs of time spent by the patient on the treatment and costs of the development of the program, while the TAU treatment requires costs related to a GP consult and/or medication. We hypothesise that from a societal perspective, these costs of the intervention CCBT are comparable to the costs of the intervention TAU. However, as a consequence of our hypothesis that CCBT is more effective than TAU, we expect that CCBT will be more preventive in health care use and productivity loss during the follow-up period, and thus result in lower costs compared with TAU by a GP. As a consequence of the expected increase of effectiveness (in terms of depression and quality of life) and decrease of costs, we hypothesise that CCBT is more cost-effective than TAU by a GP. Hypotheses about the intervention CCBT in combination with TAU are that it is both more costly and more effective compared with stand alone CCBT or TAU.

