#### Costs

Costs will be defined from the societal perspective. Within our study we distinguish three cost-categories: health care sector costs, costs for the patient and family, and productivity costs [52].

A health care use questionnaire will be developed to measure the psychological, paramedical, medical, paid and informal care, participation in a self-help group, and alternative treatments received by the patient on a monthly base. This health care use questionnaire will be based on an existing cost diary [64] and retrospective cost questionnaires [65,66], and is adapted to depressive patients. This questionnaire will provide information to calculate health care sector costs by measuring the volume of care provided, and out-of-pocket expenses, which are part of the costs for the patient and family. The other part of the patient and family costs will concern costs of travelling and lost time due to the primary care intervention TAU and/or CCBT. The time spent by a patient on CCBT will be tracked by means of the computer-registered login and logout data of the program. In the health care use questionnaire the duration of a GP consult will be registered by the patient. The number of GP consults informs on the number of travels from/to the GP, and will be linked to average distances from/to a GP. Dutch guideline prices will be used to value the costs of the health care items [67]. If for specific cost-categories cost guidelines are unavailable, average tariffs or shadow prices will be used. The standard cost prices and tariffs of health care practitioners include the integral costs, being all costs directly and indirectly attributable to the cost unit.

For the measurement of production losses, the patient modules B, C, D and E of the PROductivity and DISease Questionnaire (PRODISQ) will be used [68,69]. These modules consist of questions concerning the profession, working situation, income, absence from work, compensation mechanisms in case of absence for paid work and productivity costs at work (efficiency loss) of the patient. Productivity costs will be calculated according to the friction cost approach [67,70], using one general cost price per lost hour of productivity [67]

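### The programme cost that the plan itself names for CCBT does not appear among the cost items it measures and prices, so costs against TAU could be understated

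*Protocol article*

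**What the plan says.** **Hypothesis (Protocol article, Background, Current study).** The article states that "CCBT alone implies costs of time spent by the patient on the treatment and costs of the development of the program", whereas "the TAU treatment requires costs related to a GP consult and/or medication". From a societal perspective it expects that "these costs of the intervention CCBT are comparable to the costs of the intervention TAU". Lower later health care use and productivity loss are then expected to make CCBT the cheaper option overall.

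**Measurement (Methods, Instruments, Costs).** "Costs will be defined from the societal perspective". There are three cost categories, each with a source:
- Health care sector costs: volumes from a monthly patient questionnaire on care received.
- Patient and family costs: out-of-pocket expenses from the same questionnaire, plus "costs of travelling and lost time due to the primary care intervention TAU and/or CCBT". Time on CCBT is taken from the program's login and logout records.
- Productivity costs: a separate productivity questionnaire.

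Practitioner prices and tariffs are said to "include the integral costs, being all costs directly and indirectly attributable to the cost unit". Where no guideline price exists, average tariffs or shadow prices are used.

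**Valuation (Methods, Analyses, Economic evaluation).** The rule, applied at the level of the individual, is that "volumes of care, travels, lost time for receiving care and lost productivity hours will be multiplied by the prices determined for each cost item". The ratios compare CCBT with TAU and CCBT with the combination. Sensitivity analyses vary cost prices between minimum and maximum estimates.

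**The concern.** The hypothesis counts programme development as one of the two costs of delivering CCBT. The costing sections follow up the first cost, patient time, and do not mention the second. Researchers hand out the log-in codes (Interventions), so nothing suggests that patients would report a programme cost in the questionnaire. The adaptation of the program to ages 18 to 65 for this study has no cost item either.

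If the listed items are the ones costed, GP care carries its full direct and indirect cost and CCBT carries no programme cost. The gap would run one way: the incremental cost-effectiveness ratio, net monetary benefit and acceptability curve for CCBT against TAU would all look better for CCBT than they should. The hypothesis of comparable intervention costs could not be tested on the terms in which it is stated.

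**Working it through.** The plan gives no unit cost, development cost or expected incremental cost, so there is no figure of its own to reproduce.

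**Step 1. Items named against items costed**

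| Cost | Named in Current study | Named in Costs or Economic evaluation |
|---|---|---|
| Patient time on CCBT | yes | yes, login and logout data |
| Programme development | yes | no |
| Adaptation, hosting, maintenance | no | no |
| GP consultation | yes | yes, practitioner prices at integral cost |
| Medication | yes | not named separately; within the scope of medical care in the questionnaire |

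**Step 2. Direction**

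Let c be the programme cost per CCBT user. If it is left out:
- CCBT minus TAU: incremental cost too low by c, net monetary benefit too high by c.
- Combination minus TAU: the same error, c.
- CCBT minus combination: c − c = 0, no error.

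For an incremental effect ΔE, the CCBT versus TAU ratio shifts by c/ΔE. Bootstrapping resamples the costs that were entered, so it does not reveal a missing item. Varying the prices of entered items does not restore it either.

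**Step 3. Size, under assumptions**

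c = D/U, where D is the total development cost and U the number of users sharing it. D is assumed at 50,000 to 300,000 currency units. U = 200 is the trial's own CCBT users (100 per group, two arms; Sample size and Interventions). U = 1,000 and 10,000 are assumed.

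| Users U | c at D = 50,000 | c at D = 300,000 |
|---|---|---|
| 200 | 250 | 1,500 |
| 1,000 | 50 | 300 |
| 10,000 | 5 | 30 |

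**Step 4. Set against the document's own values**

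- The highest QALY value in the plan is £80,000. With c in pounds, 5/80,000 = 0.00006 QALY and 1,500/80,000 = 0.019 QALY.
- The Background cites an illustrative £40 per Beck Depression Inventory point. The Sample size section uses a 5-point difference. 5 × 40 = £200, so c = £200 would cancel that benefit.
- c = £200 over 200 users corresponds to D = 200 × 200 = £40,000. Over 10,000 users the same D gives 40,000/10,000 = £4.
- At an assumed gain of 0.02 QALY, c = 100 shifts the ratio by 100/0.02 = 5,000 per QALY, and c = 250 by 250/0.02 = 12,500.

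The result depends mainly on how many users share the cost, and the article gives no rule for that.

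**The case against.** The strongest reply is that the article is silent on the point and excludes nothing. Neither section says its list is closed. Volumes of care, the prices determined for each item and the shadow-price fallback are all wide enough to hold a price for a CCBT course. Naming development cost in the hypothesis even suggests an intention to count it. A journal article also commonly leaves the construction of unit prices to the full protocol, and this one gives no unit price for any item, GP consultations included.

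Much of this stands. A reader might infer that the plan values CCBT at nothing beyond patient time and that its incremental costs are therefore biased. The document does not support that. The omission is by silence, out-of-pocket expenses are counted in every arm, and the travel and time item covers both interventions. The integral-cost sentence describes practitioner prices and does not say that other items are priced at less.

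The high end of the range is also hard to defend as a base case. The program already existed, had been used in another trial, and is meant for dissemination, so charging all development to 200 trial users would overstate c.

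What remains is a mismatch within the article. It gives a source for each cost category, down to average distances to the GP and the login records, yet never returns to one of the two CCBT costs on which its hypothesis rests. The fallback could hold a programme price, but the text does not say that it does, nor how the cost would be spread.

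**Conclusion.** The concern holds in a conditional form. Followed as listed, the costing items understate the incremental cost of CCBT, and of the combination, against TAU by the programme cost per user. CCBT versus the combination and the clinical outcomes are unaffected. Bias is not established, because a programme price may be intended and is not ruled out.

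The size cannot be derived from the documents. Under the assumed development costs and user numbers it is 5 to 1,500 per user, which is negligible if thousands of users share the cost and potentially decisive if only the trial's users do. Because CCBT versus TAU is the central economic hypothesis and the answer turns on an allocation choice, that choice should be settled before results are seen.

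**What to change.** In the Costs and Economic evaluation sections, add a CCBT programme cost per user to the base case. It should cover the development cost already named in the hypothesis, the adaptation for this study, hosting and maintenance. Apply it to every patient in the CCBT and CCBT&TAU arms. State in advance the number of users over which the fixed part is spread, and vary that number within the planned minimum and maximum price sensitivity analysis. If a programme price is already intended under the shadow-price fallback, a sentence saying so and giving the allocation rule is enough.

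The cost is one item and one sensitivity analysis, with no new patient data. The institute that developed the program collaborates on the study and is the natural source for the figures. The downside is a somewhat less favourable cost result for CCBT against TAU.
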